### Ethical Considerations

This study has been approved by the Yale University Human Subjects Committee (2000040783). The study protocol was prospectively registered on the Open Science Framework on November 26, 2025. Although not required for this study type, registration was completed to support transparency and reproducibility.

We have assessed that the study poses no greater than minimal risk to participants. The key ethical issues we considered include breaches of confidentiality and exposing individuals who have never used nicotine-containing e-cigarettes to vaping-related cues.

Under Connecticut law, the legal age to purchase e-cigarettes is 21 years, and it is illegal for anyone to sell, give, or deliver e-cigarettes to individuals below 21 years [53]. As our study recruits young adults aged 18 to 21 years and assesses past substance use behaviors, participants might have to disclose underage substance use behaviors. To ensure data privacy, participants will be assigned unique study identification numbers, and substance use behaviors and physiological data will be kept separate from identifying information. The consent form will clearly state these risks and list the protections available to participants. Participants will also be reminded that they can withdraw from the study at any time and have their records removed without penalty.

For the collected data, all information will be stored on secure Yale-managed encrypted servers accessible only to approved study personnel. Identifiable information will be stored separately from study data and linked through coded participant IDs. Physiological data collected in this study include eye-gaze direction, HR, and EDA. Eye tracking records only gaze direction toward predefined regions of interest and do not capture images, video, or pupil size. HR and EDA are collected as physiological signals that do not contain identifiable biological information. Study data will be retained for a minimum of 5 years following study completion in accordance with institutional policy. Deidentified, aggregate-level data may be shared for scientific purposes upon reasonable request and institutional review board approval.

We also considered the risk of exposing nonvapers to vaping-related information. Our youth advisory group shared that exposure to vaping cues is common in their environments, such as through peers, bus stops, and social media, even for those who do not vape. In a 6-week study on social media campaigns with teens (N=415), there was no reported evidence of increased initiation risks for nonusers exposed to e-cigarette educational messages [53,54]. As such, we assess that the risk of increasing participants’ susceptibility to initiate nicotine-containing vapes is low. At the end of the laboratory visits, we will also provide all participants with a resource sheet containing support services related to substance use and well-being.

### Analysis

#### Quantitative Analysis

All data will be screened for completeness and normality before analysis. Descriptive statistics will be computed for all subjective (eg, craving, sense of presence, social presence) and physiological (eg, HR, EDA, and eye-tracking) variables. Data preprocessing will include outlier detection, missing value treatment, signal quality checks, and feature extraction to ensure valid physiological readings.

##### Primary Analyses

For the primary aim of examining differences in psychological and physiological responses between vapers and nonvapers during VR cue exposure with and without social pressure, a mixed-model ANOVA will be conducted. Group (vapers vs nonvapers) will serve as the between-subjects factor, and cue condition (social pressure vs no social pressure) as the within-subjects factor. If the assumptions of normality or homogeneity of variance are violated, nonparametric alternatives such as the aligned rank transform ANOVA [55] will be used to preserve the ability to test interaction effects within the mixed design. Follow-up pairwise comparisons will be conducted with Bonferroni-adjusted *P* values.

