#### Primary Aim

The primary aim is to examine differences in psychological (craving, sense of presence, and social presence) and physiological (eye gaze, HR, and EDA) responses between young adults who currently vape and those who have never vaped during exposure to VR vaping cues presented with and without social pressure. We hypothesize that vapers will exhibit stronger craving, a greater sense of presence and social presence, increased visual attention to vaping cues, and heightened physiological arousal compared with nonvapers across both VR scenes. We further expect that both groups will show stronger psychological and physiological responses in the social pressure condition than in the no pressure condition.

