### Study Population and Study Flow

This study will recruit young adults aged 18 to 21 years living in or around New Haven, Connecticut. Recruitment efforts will focus on two distinct groups: (1) individuals who currently use nicotine-containing e-cigarettes, defined as use on 10 days or more within the past 30 days (*vapers*), and (2) individuals who report never having used nicotine-containing vapes (*nonvapers*). Participants who use nicotine in non–e-cigarette forms (eg, cigarettes and nicotine pouches) will not be excluded but will be assessed at baseline so that such exposure can be accounted for analytically. This design allows the comparison of psychophysiological cue reactivity between vapers and nonvapers, as well as the exploration of predictors of future initiation risk among nonvapers.

Eligibility will require participants to be fluent in English and able to provide informed consent. Exclusion criteria include self-reported photosensitive epilepsy, significant visual, hearing, or mobility impairment, current or recent (past 30 days) use of cannabis-containing e-cigarettes, current use of other illicit substances (eg, 3,4-methylenedioxymethamphetamine or ecstasy, and methamphetamine), nonmedical misuse of prescription drugs, or reliance on eyeglasses that are incompatible with VR eye-tracking hardware. These exclusions help reduce noise in psychophysiological responses that may arise from nonnicotine substances, ensuring clearer differentiation between the study groups. A total sample of 40 participants will be enrolled, which is sufficient for detecting medium group effects in VR cue-reactivity studies while accounting for potential data loss.

The study flow is shown in Figure 1. Eligible participants will complete a single laboratory session lasting approximately 1 hour. After providing informed consent and completing baseline questionnaires, participants will be fitted with a VR headset and biometric sensors. They will complete 3 VR scenes: a neutral baseline, a vaping cue scene without social pressure, and a vaping cue scene with social pressure in a counterbalanced order. Physiological data will be recorded continuously, and brief self-report measures (craving, presence, and social presence) will follow each cue scene. Participants will rate the system’s usability after finishing all the VR sessions. The session will conclude with a short semistructured interview, debriefing, and compensation.

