After each VR cue scene, participants will remove the headset and complete part 2 of the assessment questionnaire. Part 2 contains self-report measures on craving, presence, social presence, and system usability. An overview of the assessment used in the laboratory visit is listed in Table 2.

**Table 2. T2:** Post–VR cue exposure measures assessing craving, presence, social presence, and system usability.

Measures	Items	Response options
Measured twice, after each VR cue scene		
Craving for vaping or smoking e-cigarettes Visual Analog Scale (VAS) [47]	1 item: “I have a desire for vaping/having an e-cigarette right now.”	A visual scale, ranging from 0 (“Not at all”) to 100 (“Extremely”)
Adapted presence and social presence questionnaire from *Presence (IPQ)* and *Social Presence by Networked Minds Measure of Social Presence* [48,49]	1 item from IPQ measuring general presence: “In the computer-generated world I had a sense of ‘being there’” (general presence item from IPQ). 6 items from the co-presence subscale (*α*=0.84). An example is: “The virtual humans caught my attention.”	5-point Likert scale, ranging from (0) “Do not agree at all” to (4) “Very Likely”
Measured once, after all VR scenes		
System usability by V*irtual Reality System Usability Questionnaire (VRSUQ)* [50]	9 items (*α*=0.679‐0.896). An example is: “The system responded well to my manipulations as expected with no delays.”	5-point Likert scale, ranging from (1) “Strongly disagree” to (5) “Strongly agree”

Eye gaze and physiological data will be recorded continuously during both VR cue scenes as follows:

Eye-gaze behavior: raw eye-tracking data and gaze fixations on predefined regions of interest (eg, vaping-related cues) will be collected and processed into fixation-related metrics such as fixation count, duration, and dwell time.HR and heart rate variability (HRV) will be monitored as indicators of autonomic arousal. HRV will be further processed into standard time-domain metrics, including the root mean square of successive differences, which reflects short-term parasympathetic activity, as well as frequency-domain metrics such as the low-frequency–to–high-frequency ratio, commonly interpreted as an index of sympathovagal balance [51].EDA will also be recorded to measure autonomic arousal and decomposed into tonic skin conductance levels and phasic SCRs using continuous decomposition analysis [52].

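### With no craving rating free of vaping cues and no stated analytic use of the neutral scene, the group main effect mixes standing vaper–nonvaper differences with cue reactivity

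*Protocol article*

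**What the plan says.** Three scenes are run. Study Population and Study Flow states: "They will complete 3 VR scenes: a neutral baseline, a vaping cue scene without social pressure, and a vaping cue scene with social pressure". Only two of them reach the stated analysis. Under Primary Analyses, "Group (vapers vs nonvapers) will serve as the between-subjects factor", and the other factor is "cue condition (social pressure vs no social pressure) as the within-subjects factor". Neither the primary nor the secondary analysis text names a change score, a baseline covariate or a third scene level.

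The rating schedule is explicit. Study Flow says that "brief self-report measures (craving, presence, and social presence) will follow each cue scene", and Table 2 heads the craving and presence items "Measured twice, after each VR cue scene". Table 1, the questionnaire given before exposure, lists no craving item.

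For the sensors, the Assessments section says "Eye gaze and physiological data will be recorded continuously during both VR cue scenes", whereas the Abstract and Study Flow describe continuous recording in a session of three scenes.

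The first hypothesis under Primary Aim is a group main effect. For arousal, vapers are expected to show "heightened physiological arousal compared with nonvapers across both VR scenes", and stronger craving is predicted in the same sentence.

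**The concern.** One group uses nicotine e-cigarettes on at least 10 of the past 30 days and the other has never used them. It is plausible that the first group reports more desire to vape before seeing any cue. Resting heart rate and skin conductance may also differ between the groups. Averaged over two cue scenes, a group difference is the sum of two parts: what was there beforehand and what the cues added. The design as written has nothing to separate them for craving, and the analysis as written does not separate them for physiology.

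The article presents its result as vaping cue reactivity and as a first step towards VR-based detection of vaping status. A main effect that can be significant with no response to the VR cues cannot carry that reading, and it could misdirect the next study. For craving, no later analysis plan can repair this, because the rating is never collected.

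**Working it through.** **Inputs from the Sample size text (Study Design).** Two groups, two cue conditions, f=0.25, r=0.50, power 0.80, minimum N=34, planned N=40 (20 per group). Alpha is not stated; two-sided 0.05 is assumed throughout.

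**1. The plan's own figure.** For the within–between interaction, λ = N·m·f²/(1−r) with m=2 scenes and df = 1, N−2.
- N=32: λ = 32×2×0.0625/0.5 = 8.0, power 0.781.
- N=34: λ = 8.5, power 0.807.
- N=40: λ = 10.0, power 0.869.

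The minimum even N is 34, as stated. The sample size is not in error, and this point does not depend on it.

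**2. Group main effect with zero cue reactivity.** Take unit SD in each scene, equal correlation r among the three scenes, and the same group offset δ in all three. The mean of two cue scenes has variance (1+r)/2, which is 0.75 at r=0.50. With n=20 per group the noncentrality is δ/√(2×0.75/20) = δ/0.2739 on 38 df. The documents give no value for δ, so a range is assumed.

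| Standing offset δ (SD) | Noncentrality, r=0.50 | Significant, r=0.50 | Significant, r=0.70 |
|---|---|---|---|
| 0.5 | 1.83 | 43% | 39% |
| 0.8 | 2.92 | 81% | 76% |
| 1.0 | 3.65 | 94% | 92% |

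A simulation of 20,000 studies gave 43%, 82% and 95% at r=0.50. In the same runs, cue mean minus neutral was significant in about 5% for every offset, and so was the group × cue condition interaction. The offset is a constant, so both differences remove it.

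**3. Price of the baseline-corrected contrast.** Cue mean minus neutral has variance (1+r)/2 + 1 − 2r. For a true reactivity difference of 0.5 SD and n=20 per group:

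| r | Variance, uncorrected | Variance, change | Power, uncorrected | Power, change |
|---|---|---|---|---|
| 0.3 | 0.65 | 1.05 | 48% | 32% |
| 0.5 | 0.75 | 0.75 | 43% | 43% |
| 0.7 | 0.85 | 0.45 | 39% | 63% |
| 0.8 | 0.90 | 0.30 | 37% | 80% |

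At the plan's own r the two tests have equal power. The gain appears only above 0.50, and the documents do not give a higher value.

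**The case against.** Several objections have force.

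- **The test that was powered is the interaction.** A constant offset cancels there, so the powered result is not distorted. That stands. But the interaction asks whether the groups respond differently to social pressure, in two scenes that the article itself says are not fully context-matched. It does not ask whether vaping cues move vapers more than a neutral scene does.
- **The article is silent on baseline correction of physiology, which is not the same as choosing raw levels.** A reader might infer that uncorrected heart rate and electrodermal levels will be analysed. The text does not say so, and a fuller plan may specify a correction. For physiology the point is therefore conditional. For craving it is not, because the rating schedule is stated.
- **A reader might infer that the group comparison measures standing differences instead of reactivity, across all primary outcomes.** The documents do not support that. The main effect contains both parts. Gaze on vaping regions exists only where cues are shown, and presence and social presence are ratings of a scene, so these outcomes are largely unaffected.
- **A reader might also expect a clear gain in precision.** At r=0.50 there is none.
- **The corrected contrast has low power: 43% for 0.5 SD.** This is true and should be stated. The interaction's 87% at N=40 is not directly comparable, since f=0.25 in a 2×2 layout means a between-group difference in scene change of 4×0.25 = 1.0 SD. Even so, the contrast should sit beside the powered interaction and not replace it.
- **This is a pilot.** That limits the consequences, but the article's Limitations do not mention the problem, and the missing rating takes one item.

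**Conclusion.** The point holds in a bounded form. For craving, the planned group main effect cannot distinguish a standing vaper–nonvaper difference from reactivity to the VR cues, because no rating free of vaping cues is scheduled. For heart rate, its variability and electrodermal activity the same is true unless the features are baseline-corrected, which the article does not say. It is also unclear whether these signals are recorded in the neutral scene at all.

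The size depends on an offset that the documents do not give. Over an assumed 0.5 to 1.0 SD, with no cue reactivity and r=0.50, the group test is significant in about 43% to 94% of studies, against a nominal 5%. The calculation further assumes equal variances, equal correlation among scenes, an offset constant across scenes, and all 40 participants analysable. The sample size calculation and the powered interaction are not called into question.

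**What to change.** 1. For all remaining participants, give the one-item craving visual analogue scale after the neutral scene, and run that scene before either cue scene.
2. Reconcile the Assessments sentence on recording during both cue scenes with the Abstract and Study Flow, and state that physiology is recorded in the neutral scene.
3. For craving, heart rate and its variability, and electrodermal activity, test the group difference in cue reactivity by the group × (mean of cue scenes minus neutral) contrast. Keep the group × cue condition interaction as planned. Report the uncorrected group main effect descriptively and not as evidence of cue reactivity. Gaze on vaping regions and the presence ratings can stay as cue-scene outcomes.

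**Costs.** One extra item per session and an edit to the analysis text. Those already run (7 participants as of March 2026) will lack neutral-scene craving; whether their neutral-scene physiology exists depends on step 2. The contrast has about 43% power for a 0.5 SD reactivity difference at r=0.50, more at higher r and less below, and the article should say so. With neutral always first, cue versus neutral is partly confounded with time in session. The comparison of that change between groups is less affected.

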## Methods

### Study Design

This study will examine individuals’ psychological, behavioral, and physiological responses to e-cigarette cues in VR among young adults aged 18 to 21 years. We focus on this age range because the transition into early adulthood often brings increased exposure to vaping-related social contexts (eg, college gatherings) [27], and this pilot allows us to first test the paradigm in adults before adapting it for adolescent populations. A between-subjects design is used to compare current e-cigarette users and nonusers, with a within-subject, counterbalanced component to assess 2 cue conditions (with and without social pressure). This mixed-design approach enables testing of cue effects and group differences while controlling for individual variability.

Prior VR nicotine cue reactivity studies have reported medium-to-large effects for the response difference between user and nonuser groups [17,28]. Based on the relevant research and using G*Power 3.1 (Heinrich Heine University Düsseldorf) for a 2 (group: vapers vs nonvapers)×2 (cue condition: social pressure vs no social pressure) mixed design, we powered the study for the group × cue condition interaction (group×cue condition) assuming a medium effect (*f*=0.25; partial η-squared ≈ 0.06; power=0.80). We assumed a within-participant correlation of *r*=0.50 between cue conditions and a nonsphericity correction of *ε*=1.0 (sphericity is not applicable with 2 within-subject levels). This yields a minimum required sample of 34 (n=17 per group). To ensure robustness and account for potential data loss (eg, eye-tracking dropout and physiological artifacts), we plan to recruit 40 participants in total (n=20 vapers and n=20 nonvapers).

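### The named fallback for unequal variances, aligned rank transform ANOVA, does not correct unequal variance and can inflate false positives for the craving interaction and scene tests if never-vapers sit near zero

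*Protocol article*

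**What the plan says.** The Primary Analyses section plans one mixed ANOVA for all primary-aim responses: "Group (vapers vs nonvapers) will serve as the between-subjects factor, and cue condition (social pressure vs no social pressure) as the within-subjects factor". It then sets a switch: "If the assumptions of normality or homogeneity of variance are violated, nonparametric alternatives such as the aligned rank transform ANOVA [55] will be used". The stated reason is "to preserve the ability to test interaction effects within the mixed design". No other alternative is named.

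The Study Design section makes the interaction the effect that sets the sample size: "we powered the study for the group × cue condition interaction".

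Craving is among the responses listed under the Primary Aim. Table 2 measures it with one item, "I have a desire for vaping/having an e-cigarette right now", on a 0-100 visual scale after each cue scene. Both groups answer it. One group vaped on at least 10 of the past 30 days; the other consists of "individuals who report never having used nicotine-containing vapes".

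**The concern.** The switch has two triggers, non-normality and unequal variance. ART was built for the first. It removes the effects not under test, ranks what is left, and runs an ordinary ANOVA on the ranks. Nothing in that sequence equalises the spread of two groups.

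Craving is where this matters most. If many never-vapers answer at or near 0 while vapers spread over the scale, the variances differ and the rule leaves the ordinary ANOVA. In a balanced 2×2 design that ANOVA is close to its nominal level under such heterogeneity. The rule would then exchange a roughly valid test for an invalid one, for a primary-aim outcome and for the effect on which the study is powered.

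**Working it through.** **1. The plan's own figure.** For the within-between interaction, λ = f²·N·m/(1 − r), with f = 0.25, m = 2 scenes, r = 0.50 and df = (1, N − 2). Alpha is not stated; 0.05 is assumed. At N = 34, λ = 0.0625 × 34 × 2 / 0.50 = 8.5 and power is 0.807. At N = 32, λ = 8.0 and power is 0.781. The stated minimum of 34 is reproduced. At N = 40, λ = 10 and power is 0.869. So the sample size is sound for the ordinary ANOVA; the question is what happens after the switch.

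**2. Why ART fails at a floor.** The aligned score is A = y − (cell mean) + (estimated effect under test). Suppose all 20 never-vapers score 0 in both scenes, and vapers have cell means a and a + d, where d is pure chance.
- Grand mean: (2a + d)/4.
- Interaction estimate for never-vapers, first scene: 0 − 0 − a/2 + (2a + d)/4 = +d/4. Second scene: −d/4.
- Their residuals are 0, so all 20 never-vapers have A = +d/4 in one scene and −d/4 in the other.
- Two tied blocks of 20 have mid-ranks that differ by 20 plus the number of vaper scores lying between them. The gap is therefore at least 20 of 80 ranks, however small d is, and it has no variance within the group.

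The rank ANOVA reads this as a consistent effect. The scene estimate is also ±d/4, so the scene main effect behaves almost identically.

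**3. Why the ordinary tests hold.** In a 2×2 mixed design the interaction F is the square of a t-test on within-participant scene differences. With n per group, the pooled variance of the contrast is [(s₁² + s₂²)/2] × (2/n) = (s₁² + s₂²)/n, which is the Welch variance. Only the degrees of freedom differ.

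**4. Size, by simulation.** Assumed, because the protocol gives no craving means, SDs or share at zero: 20 per group; vapers mean 45, SD 25; within-person r = 0.5; never-vapers exponential with scale 8, a given share of them set to zero; no scene or interaction effect; nominal 5%.

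| Never-vapers at zero | ART, interaction |
|---|---|
| 0% | 16% |
| 30% | 25% |
| 50% | 35% |
| 70% | 55% |
| 90% | 84% |

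Across these rows the ordinary ANOVA gave 5.5-6.7% and Welch on differences 5-6%. Separately coded simulations agree within a few percentage points. With every never-vaper at zero, ART reached 94-95%. With 17 per group and the same scenarios it gave about 15-76%.

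**5. Milder cases, ART interaction error.**
- Exponential scale 15, no excess zeros: about 7-9%; with half at zero, about 26%.
- Clipped normal, mean 20, SD 15: 8%; mean 25, SD 20: 5%.
- Unequal variance alone (normal, no floor): SD ratio 1.5 gives 6%, 2 gives 7%, 4 gives 15%, 10 gives 37%.

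**6. Would the trigger fire?** A median-centred Levene-type test of equal variance fired in 86-100% of near-zero data sets, in 76-81% at scale 15, and in 30% at mean 25, SD 20. In the near-zero data sets, ART's error rate given that the trigger fired was essentially unchanged.

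**The case against.** **The inputs are assumed.** The protocol gives no craving distribution. Nonvapers who use cigarettes or nicotine pouches are not excluded, and both groups are expected to respond more under social pressure, so never-vapers may not sit at zero. This stands. A reader might infer that the floor is certain, or that ART has one fixed error rate; the document supports neither, and where never-vapers spread well above 0 the inflation is small or absent.

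**ART is only an example.** The text says such as, and a separate analysis plan may settle the method by outcome. True, but ART is the only method named, and unequal variance is an explicit trigger for it. As written, the rule points the wrong way.

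**Other outcomes.** Presence, social presence, gaze, heart rate and electrodermal activity fall under the same rule, and a reader might infer that ART is unsuitable for all of them. That is not shown. With skewed lognormal data and identical groups, ART held 5.6% while the ordinary ANOVA was conservative at 2.8%.

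**Direction and visibility.** One might infer that the method would manufacture the predicted social-pressure effect. Under the null the chance effect has random sign, so false positives point either way. The planned descriptive statistics would also show a trivial raw difference beside a significant rank test. That softens the harm but does not restore the test's level.

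**Pilot status.** The explicit call for cautious interpretation is in Secondary Analyses and concerns the regularized regression, not these primary tests.

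**Conclusion.** The point holds for the craving interaction and scene tests. ART does not correct unequal variance, yet unequal variance is one of the two conditions that call for it. At nominal 5% and 20 per group, its false-positive rate runs from about 5-10% (never-vapers well above 0), through about 16-35% (scale 8, 0-50% at zero), to over 80% (90% at zero). The ordinary ANOVA and Welch tests stay at about 5-6%.

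The mechanism is certain. The percentages are scenarios that rest on assumed craving distributions and on alpha 0.05. The vaper-nonvaper main effect is not implicated: in these scenarios the groups truly differ, so its rejections are not false positives.

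**What to change.** State that unequal variance is not a reason to switch to ART. For craving, and for any other outcome with clearly unequal group variances or a floor in one group, prespecify the following, where d̄ is the group mean and s² the group variance of within-participant scene differences (V vapers, N never-vapers):
- **Interaction:** Welch t-test on the differences, t = (d̄_V − d̄_N) / √(s_V²/n_V + s_N²/n_N).
- **Scene effect:** the equally weighted mean (d̄_V + d̄_N)/2, with standard error ½√(s_V²/n_V + s_N²/n_N).
- **Group effect:** Welch t-test on participant means.

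Keeping the planned ANOVA is an acceptable alternative while group sizes are equal; exclusions could make them unequal, which favours Welch. Any permutation or bootstrap check should be studentized, because plain label permutation assumes exchangeability, which unequal variances break. ART may stay for non-normal outcomes with similar group spread.

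The cost is analysis wording; no data or participants are added. With similar spreads Welch loses almost no degrees of freedom. If one group has no variance at all, they fall from 2 × 20 − 2 = 38 to 20 − 1 = 19, and the two-sided 5% critical value rises from 2.02 to 2.09. With 7 of 40 participants' data collected as of March 2026, the change can still be made before analysis.

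### No outcome or effect is designated primary among six outcome domains and three ANOVA effects, and the one stated correction, Bonferroni on follow-up comparisons, does not cover multiplicity across them

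*Protocol article*

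**What the plan says.** The Primary Aim section sets out to examine "differences in psychological (craving, sense of presence, and social presence) and physiological (eye gaze, HR, and EDA) responses" between vapers and nonvapers, so six domains sit under the primary aim. It attaches two sets of directional hypotheses to them. One is a group effect, for example "heightened physiological arousal compared with nonvapers across both VR scenes". The other is a scene effect: "both groups will show stronger psychological and physiological responses in the social pressure condition than in the no pressure condition".

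The Study Design section bases the sample size on a third effect: "we powered the study for the group × cue condition interaction". It assumes f=0.25, within-participant correlation 0.50 and power 0.80, which gives N=34, raised to 40.

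The Assessments section divides the physiological domains further. Gaze data, for instance, are "processed into fixation-related metrics such as fixation count, duration, and dwell time".

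Under Primary Analyses, "a mixed-model ANOVA will be conducted" with group and cue condition as factors. The only multiplicity provision is "Follow-up pairwise comparisons will be conducted with Bonferroni-adjusted" P values. The article states no significance level, and it does not rank the outcomes or the effects. The Limitations section calls eye gaze direction one of the primary outcome measures, which confirms that there are several.

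**The concern.** A 2×2 mixed ANOVA gives three F-tests per outcome: group, condition and interaction. Both factors have two levels, so each main-effect F-test already is the pairwise comparison, and no follow-up is needed. Bonferroni on follow-up comparisons can therefore act only on simple effects after an interaction. It does nothing across the six domains or across the three effects, which is where most of the multiplicity lies.

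Two things are at stake. First, with no designated primary test, an isolated significant result among 12 to 18 tests cannot be told apart from chance. The article wants its findings to guide VR-based risk tools and extension to younger adolescents, so a false marker could carry forward. Second, the power calculation describes a single interaction test on a single unnamed outcome, while the stated hypotheses concern the two main effects on six domains. The power figure does not match how the primary aim is framed.

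**Working it through.** **Inputs.** Six domains and two hypothesised main effects come from Primary Aim. The powered interaction, f=0.25, r=0.50, power 0.80, N=34 and N=40 come from Study Design. Alpha is not stated.

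**1. Reproduce the plan's figure and infer alpha.** For the within-between interaction with m=2 measures, λ = f²·N·m/(1−r), with 1 and N−2 degrees of freedom.
- N=34: λ = 0.0625×34×2/0.5 = 8.5; power at alpha 0.05 is 0.807.
- N=32: λ = 8.0; power is 0.781.

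The smallest balanced sample is therefore 34, as stated. With the other inputs unchanged, alpha 0.10 would give 28 and alpha 0.025 would give 42. So 0.05 for a single test is an inference, but a firm one.

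**2. False-positive rate if the tests are independent.** With k tests at 0.05 and no true effects, the rate is 1 − 0.95^k.
- One effect × six outcomes, k=6: 1 − 0.95^6 = 0.265
- Two hypothesised main effects, k=12: 1 − 0.95^12 = 0.460
- All three effects, k=18: 1 − 0.95^18 = 0.603

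**3. Allow for correlated outcomes.** The article gives no between-outcome correlation, so a range is assumed. The 2×2 mixed ANOVA was simulated with 20 per group, within-person correlation 0.5, equal correlation between all outcomes, two-sided tests and no true effects.

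| Between-outcome correlation | One effect (6 tests) | Two main effects (12 tests) | All three (18 tests) |
|---|---|---|---|
| 0 | 26% | 46% | 60% |
| 0.3 | 24% | 42–43% | 56–57% |
| 0.5 | 21% | 37% | 50–51% |
| 0.7 | 17% | 30–31% | 42% |
| 0.9 | 11% | 21% | 29–30% |

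Every cell is above 5%.

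**4. Power consequences of choosing one effect.** For the group effect, λ = f²·N·m/(1+r). At N=40 this is 0.0625×40×2/1.5 = 3.33. For the interaction at N=40, λ = 10.

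| Alpha | Interaction power, N=40 | Group-effect power, N=40 |
|---|---|---|
| 0.05 | 0.87 | 0.43 |
| 0.01 (= 0.05/5) | 0.67 | 0.20 |
| 0.0083 (= 0.05/6) | 0.65 | 0.19 |

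**The case against.** **The sentence on Bonferroni is not wrong, and the rest may be in a plan not shown.** Bonferroni suits simple effects after an interaction, and choosing a metric per domain is commonly left to an analysis plan. That holds for the fine detail. But the article itself makes all six domains primary, powers an effect it does not hypothesise, and places its one correction where this multiplicity is not. A later plan would have to settle a hierarchy that the article leaves open while calling several outcomes primary.

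**The study is a pilot.** Strict family-wise control in a pilot is partly a matter of preference, and labelling most tests exploratory would be an acceptable answer. The article does not do that. Its caution about exploratory interpretation is attached to the regularized regression, not to the primary ANOVAs, which carry directional hypotheses and a formal power calculation.

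**A flat 50–60% overstates the case.** This stands. A reader might infer that the study has a 50–60% chance of a false primary finding. That figure needs all three effects counted, no true effects and between-outcome correlation of at most about 0.5. The interaction is powered but not hypothesised. The hypotheses are directional, so counting only results in the predicted direction gives 1 − 0.975^12 = 26% for the 12 main-effect tests and 1 − 0.975^6 = 14% for the group effect alone, if independent. Some effects are probably real: craving should differ between people vaping on at least 10 of 30 days and people who have never vaped, and social presence should differ between a party and a shopping task. Each real effect removes a true null and lowers the rate.

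**Two further inferences are not supported.** A reader might assume that any single significant test would be reported as success; the article states no success rule, and its hypotheses describe a joint pattern. A reader might also multiply by the number of metrics, giving up to 79% for ten metrics and three effects (1 − 0.95^30 = 0.785). The article lists metrics as recorded features and regression candidates, but does not say that each gets a primary ANOVA.

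**Conclusion.** The point holds as a structural one. Six domains and three effects fall within the primary analysis, none is designated primary, and the stated correction does not reach multiplicity across outcomes or effects. With alpha 0.05 per test (inferred from N=34), two-sided tests, no true effects and between-outcome correlation from 0.5 to 0, the chance of at least one false-positive primary test is about 21–26% for one effect, 37–46% for the two hypothesised main effects and 50–60% for all three. These are conditional figures, not the probability that the study reaches a false conclusion. That probability depends on a success rule the article does not give. The matter should be corrected, and it is cheap to correct at this stage.

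**What to change.** In Primary Analyses and in the registration:

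1. Prespecify one metric for each of the six domains.
2. Name one primary outcome and one primary effect, tested at 0.05, and state the alpha. There are two ways to choose the effect. Keeping the interaction preserves the stated power (0.81 at N=34, 0.87 at N=40), but the Primary Aim then needs an interaction hypothesis. Choosing the group contrast fits the hypotheses, but power must be restated as about 0.43 at N=40 under the same f=0.25 and r=0.50. The statement under Study Population that 40 suffices for medium group effects must then be revised.
3. Test that same effect on the other five domains by Holm (first step 0.05/5 = 0.01), only if the primary test is significant. The gate matters: an ungated Holm family beside a separate 0.05 test could total 1 − 0.95² = 9.75% if independent. Alternatively, name no single outcome and apply Holm across all six (first step 0.05/6 = 0.0083).
4. Report the other effects and metrics as secondary or exploratory, with confidence intervals.
5. Keep Bonferroni for simple effects after an interaction.

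**Cost.** A paragraph of text and a registration update, with data from 7 of 40 participants collected as of March 2026. The non-primary outcomes face stricter thresholds and lower power: interaction power at N=40 is 0.67 at alpha 0.01 and 0.65 at 0.0083. Any stated hypothesis that is not chosen, such as the scene effect, loses its primary status.
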